### Sample size (14)

We will utilize an alpha of .025 to account for our two co-primary outcomes. Our sample will include 500 participants in the PrEP component and approximately 240 in the HCV component. We estimated power using a simulation program written for SAS 9.4. This program generated data with various constellations of treatment effects, site effects, venue effects, and interactions. A simple power analysis shows that with 500 participants and alpha = .025 that there is 90% power to uncover an absolute difference of approximately 15% (40% versus 55.5%, RR = 1.40) for main effects of the treatment arm (across site and venue). This power statement assumes that response rates are at the point of highest variance in the binomial distribution—i.e., variance decreases causing power to increase if the probabilities are actually further from .5 in either direction. We anticipate larger absolute differences but have kept the simple power high to account for the potentially complex interactions we might see. For example, with this sample size, the power for the primary (PrEP) outcome is about 86.8% when there are differences in site and venue of 13% and 16% respectively, and when power for the site and venue differences is greater than 80%. There is better than 80% power for an interaction effect (e.g., site by treatment) with a rate ratio [RR(site 1)/RR(site2)] of at least 1.37. Power for effects within a site or venue is around 90% for an absolute risk difference of .22 (40% versus 62%). Note that planned tests of differences (i.e., interactions) by the biological variable, sex, would need to have a rate ratio of 1.5 to have 80% power. For HCV outcomes, the sample size is expected to be smaller (*n* = 240); for the HCV primary hypothesis, there is 90% power to uncover an absolute difference of 21% (40% versus 63%, RR = 1.58), well within the range of what we expect for this intervention [63]. This is based on the extremely low rates of PrEP currently in our candidate venues and the relatively high rate of continuation (58%) in the open-label extension of the Bangkok Tenofovir Study where PrEP was provided without cost as is the case in the current protocol [63].

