## Assignment of interventions: allocation

### Sequence generation (16a)

Participants are randomized to one of two treatment groups in a 1:1 ratio. Randomization at the individual level uses a permuted-block randomization scheme to ensure relative balance across time; the block size is randomly permuted to prevent study staff from guessing the block size and inferring the condition to which the next participant will be assigned. Randomization tables have been generated by study statisticians separately for venues within site and by HCV antibody status.

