## Statistical methods

### Statistical methods for primary and secondary outcomes (20a)

The *primary hypothesis* is that on-site integrated care is superior to off-site referral with patient navigation in achieving higher rates of sustained PrEP adherence and/or HCV cure, measured as the proportion of participants achieving detectable levels of tenofovir in DBS in the first 6 months of follow-up and achieving HCV sustained virologic response 12 weeks post-treatment completion after initiating treatment within the 6 months post-randomization. A sub-hypothesis is that the difference in rates of sustained PrEP adherence and HCV cure with on-site integrated care relative to referral with patient navigation will be moderated by healthcare system and venue; differences between on-site versus referral will be greater in Miami vs. Montreal and in SSP vs. OAT settings. For the *primary hypothesis*, each of our two co-primary outcomes, sustained PrEP adherence and HCV cure, will be tested at an alpha rate of .025 using a Poisson regression analysis with a binary outcome to directly estimate the risk ratio associated with on-site integrated care (rather than the odds ratio estimated by logistic regression). Both co-primary hypothesis tests will be stratified by site and venue, testing for interactions of treatment effect by site and venue due to our expectation that context is important for implementation. In the absence of qualitative interaction effects, the main effects will be examined.

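### Testing each co-primary at a fixed .025 is valid but conservative; Holm at the same 5% family-wise error would add about 3 to 4 points of power per outcome

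*Protocol article*

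**What the plan says.** Two sections of the protocol article fix the test level, and they agree.

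- Sample size (14): "We will utilize an alpha of .025 to account for our two co-primary outcomes".
- Statistical methods for primary and secondary outcomes (20a): each co-primary "will be tested at an alpha rate of .025 using a Poisson regression analysis".

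Section 20a also states the hypothesis so that one outcome is enough to support it: on-site care is expected to be superior "in achieving higher rates of sustained PrEP adherence and/or HCV cure".

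The power figures come from Sample size (14). "Our sample will include 500 participants in the PrEP component and approximately 240 in the HCV component". For PrEP, "there is 90% power to uncover an absolute difference of approximately 15% (40% versus 55.5%, RR = 1.40"). For HCV, "there is 90% power to uncover an absolute difference of 21% (40% versus 63%, RR = 1.58").

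Interim analyses (21b) plans no efficacy or futility look, so no alpha is spent elsewhere. The article states no step-down rule and no rule for passing alpha from one co-primary to the other.

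**The concern.** When either outcome can support the hypothesis and each is tested at .025, the procedure is unweighted Bonferroni. Once one null hypothesis has been rejected at .025, only the other remains, and it can be tested at the full .05 with family-wise error still at or below .05. The plan does not use this.

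The consequence shows in a concrete case. With PrEP p = .01 and HCV p = .04, the present text declares HCV not significant, although a procedure with the same 5% family-wise error would reject both. The objectives ask about both outcomes, so power for each, and for both together, matters to what the trial can conclude. This does not depend on detail left to an analysis plan: the article itself fixes the .025 level, and an analysis plan that follows it would carry the same loss.

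**Working it through.** **Inputs.** Sample size (14): PrEP N = 500, 40% versus 55.5%; HCV N about 240, 40% versus 63%; alpha .025. Sequence generation (16a): "Participants are randomized to one of two treatment groups in a 1:1 ratio", taken here as 250 and 120 per arm. Two assumptions are not in the article. Sidedness is not stated; two-sided is used because it reproduces the stated power. The correlation between the two tests is not given; 0, 0.3 and 0.5 are used.

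**Step 1: reproduce the stated 90%.** Power = Φ[(d − z·s0)/s1], where s0 is the pooled and s1 the unpooled standard error of the difference d, and z = 2.2414 for two-sided .025 or 1.9600 for two-sided .05.

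| Outcome | d | s0 | s1 | Power at .025 | Power at .05 |
|---|---|---|---|---|---|
| PrEP, 40% vs 55.5%, 250 per arm | .155 | .04468 | .04414 | Φ(1.243) = .893 | Φ(1.528) = .937 |
| HCV, 40% vs 63%, 120 per arm | .23 | .06452 | .06279 | Φ(1.360) = .913 | Φ(1.649) = .950 |

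Both powers at .025 are within 2 points of the stated 90%. One-sided .025 would give 93.7% and 95.0%, which fits less well.

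**Step 2: Holm with independent tests.** Write P and H for the PrEP and HCV powers, with the level as subscript.

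- HCV: H.025 + P.025 × (H.05 − H.025) = .913 + .893 × (.950 − .913) = .946
- PrEP: P.025 + H.025 × (P.05 − P.025) = .893 + .913 × (.937 − .893) = .933
- Both, fixed split: .893 × .913 = .815
- Both, Holm: P.025·H.05 + H.025·P.05 − P.025·H.025 = .889
- At least one, either procedure: 1 − (1 − .893)(1 − .913) = .991

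The gain is 4.0 points for PrEP, 3.3 for HCV and 7.3 for both. It is zero for at least one, because Holm's first step is the Bonferroni test.

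**Step 3: correlated tests.** HCV participants are a subset of the 500, so independence is not assured. Simulation used 4 million bivariate normal draws per scenario, with means matched to the .025 powers.

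| Correlation | PrEP, fixed → Holm | HCV, fixed → Holm | Both, fixed → Holm | At least one, either procedure |
|---|---|---|---|---|
| 0 | 89.3 → 93.3% | 91.3 → 94.6% | 81.5 → 88.8% | 99.1% |
| 0.3 | 89.3 → 92.9% | 91.3 → 94.2% | 82.7 → 89.2% | 98.0% |
| 0.5 | 89.3 → 92.7% | 91.3 → 93.9% | 83.6 → 89.7% | 96.9% |

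The 0.1-point gap from Step 2 for both outcomes at correlation 0 comes from matching the means only at the .025 level.

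**Step 4: error rates.** With both nulls true, the simulated family-wise error is the same for the two procedures (4.6 to 4.9%). With one null true and the other outcome at its planned effect, the false-rejection rate for the null outcome is 2.5% under the fixed split and at most 4.8% under Holm in these runs. The theoretical ceiling is 5%.

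**Step 5: the 21-point figure.** Sample size (14) calls 40% versus 63% a 21% difference, but 63 − 40 = 23. The stated ratio of 1.58 fits 63% (63/40 = 1.575) and not 61% (61/40 = 1.525), and the stated 90% power also fits 63% better. If 61% were nevertheless the intended rate, HCV power would rise from 85.0% to 89.4-90.0%, and power for both from 75.9-78.8% to 84.5-86.0%, over the same correlations.

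**The case against.** The strongest case against acting is that nothing here is wrong. The two sections agree, total alpha is 5%, the sample size was built for .025, and each outcome already has about 90% planned power. A conservative split is a legitimate choice. All of that stands, and it limits the point to an efficiency gain. A reader might infer that the multiplicity control is faulty or that type I error is inflated; the article does not support that.

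A second objection is that, under a hypothesis that one outcome can satisfy, Holm gains nothing. For the chance of at least one success this is exactly right. A reader might infer that Holm makes a positive trial more likely; it does not. The gain is in power for each outcome and for both, which remains relevant because the objectives name both.

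Third, a reader might expect the smaller HCV component to benefit most. At the stated rates PrEP gains slightly more (4.0 against 3.3 points with independent tests). HCV gains more only at 61%, which rests on the 21% figure that conflicts with the same sentence's rates and ratio.

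Fourth, Holm has a price. With fixed .025 tests, a 97.5% interval for each risk ratio corresponds directly to its decision; under Holm the two can disagree. The protection of each outcome taken singly also weakens, as Step 4 shows. Both are real but small, and family-wise error stays within 5%.

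Finally, the power figures are approximate. The planned test is Poisson regression stratified by site and venue, and Sample size (14) itself gives 86.8% PrEP power in one scenario with site and venue differences. The exact gain will differ. The ordering will not, because Holm rejects everything the fixed split rejects whatever the test.

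**Conclusion.** The point holds as a cheap improvement. The fixed .025 split is valid but conservative, and Holm is uniformly at least as powerful at the same 5% family-wise error, with no extra participants. At the plan's own rates the gain is about 3 to 4 points for each outcome and about 6 to 7 points for winning both; it is nil for winning at least one. These sizes rest on two-sided tests, 1:1 arms of 250 and 120, an unadjusted two-proportion approximation, true rates equal to those planned, and a correlation between 0 and 0.5. No conclusion of the trial would be biased or invalid if the split were kept.

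**What to change.** Before unblinding, add one sentence to section 20a or to the analysis plan: the two co-primary p-values are tested by Holm's procedure, the smaller at .025 and, if that is significant, the larger at .05. Blinding (17a) says analysis plans will be finalized before the data are locked and that the study statistician stays blinded, so this can still be done properly.

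Leave the sample-size statement at .025 and describe it as conservative.

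State in advance how intervals will be reported, for example 97.5% intervals for each risk ratio with a note that they may not match every Holm decision. The cost is that sentence and that note, plus the weaker single-outcome error protection described above; no change to enrolment or data collection is needed.

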### Objectives (7)

The primary study objective is to compare the effectiveness of on-site integrated care that includes adherence counseling vs. off-site referral to care with support of a patient navigator in increasing rates of (1) PrEP adherence (0–6 months) and (2) HCV sustained viral response 12 weeks post-treatment completion (SVR12) among PWID recruited in OAT and SSP in Miami, FL, and Montreal, Quebec. The study will examine the relative contributions of living in cities with different healthcare systems (Miami vs. Montreal) and venues (OAT vs. SSP) on primary outcomes.

Secondary objectives are to measure differences between study arms in (1) PrEP initiation, (2) long-term sustained PrEP adherence (6–18 months), (3) HCV infection/reinfection, (4) sexually transmitted infections and reinfection (including HIV), and (5) behavioral disinhibition, i.e., the proportion of participants who increase sexual or injection risk behaviors.

The study will include a qualitative component with the following objectives: (1) to explore individual and structural factors influencing PrEP initiation and adherence; (2) to examine how PWID understand and define PrEP adherence; (3) to describe and understand PWID’s experience regarding on-site and off-site interventions including their perceived effects on PWID’s health; (4) to examine if and understand how PrEP use is related to HIV risk behavior modifications among PWID; (5) to understand facilitators and barriers to implementation and how study staff experience and address these factors during the trial.

Finally, a cost-effectiveness analysis will evaluate (1) healthcare services utilization and cost-effectiveness of the on-site integrated care approach compared to the referral with patient navigator and (2) the healthcare resources required to scale up these intervention approaches in the local environments and site settings.

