### Outcomes (12)

#### Primary outcome measures

The co-primary trial outcomes are (1) sustained PrEP adherence during the first 6 months and (2) HCV cure among participants living with HCV.

**Table 4 Tab4:** Definition and measure of secondary and tertiary outcomes

Secondary outcomes	Definition	Measure
PrEP initiation/uptake	Receiving a prescription and taking the first dose of the medication	First dose of Rx dispensed to the patient and recorded at pharmacy/dispensing venue + self-report
Long-term sustained PrEP adherence	PrEP use at 6, 12, and 18 months post-randomization	Self-report + detectable level of TDF in DBS 6, 12, and 18 months post-randomization
HCV incidence/re-infection	New HCV infection	At scheduled visit: HCV-Ab positive (never infected) or detectable HCV-RNA (previously infected and cured)
STI or HIV incidence/STI re-infection	New STI or HIV infection in a previously uninfected person/previously infected and cured person	At scheduled visit: Any positive test result for *Neisseria gonorrheae*, *Chlamydia trachomatis*, syphilis, or HIV
Behavioral disinhibition	Changes or increase in sexual or injection risk behaviors	Self-report at each visit
**Tertiary outcomes**	**Definition**	**Measure**
Ongoing PrEP use	Any PrEP use during any period	Any detectable level of TDF in DBS/Self-report of use
HCV SVR within those initiating	12-week sustained viral response post-end of treatment	First dose of medication dispensed to the patient and recorded at pharmacy/dispensing venue + self-report/HCV-RNA negative at 12 weeks post end of treatment

Sustained PrEP adherence will be compared between both treatment arms at 6 months post-randomization. Sustained PrEP adherence will be defined as the self-report of achieving daily PrEP use, which will be confirmed by evidence of detectable levels of tenofovir. In order to achieve protection against HIV infection, TDF/FTC should be taken once daily to achieve protective levels. PrEP use will be self-reported by participants. Blood tenofovir will be detected using DBS collected every month beginning at 8 weeks post-PrEP initiation during the first 6 months post-randomization and subsequently every 3 months during research visits.

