We will analyze long-run sustained PrEP adherence and HCV cure resulting from treatment initiated after the first 6 months, similarly, except using a repeated-measures Poisson regression implemented as a generalized estimating equation (GEE) including the periods between 6- and 18-month follow-ups. It is important to note that for all PrEP adherence analyses, any participants who become HIV positive will be counted as PrEP non adherent. For all other secondary outcomes, similar approaches will be used. PrEP initiation will be assessed as a simple binary outcome (initial self-reported use verified by prescription in medical records) and again modeled using repeated measures Poisson regression. We will examine sustained PrEP adherence among those self-reporting taking PrEP to disentangle PrEP non-engagement, inadequate PrEP use, and protective levels of PrEP use. Note that protective levels of PrEP use will be examined only among patients not on HCV medication due to norms for protective PrEP use when taken with HCV medication not having been established. We will examine HCV treatment initiation and rates of SVR among those treated (the primary analysis will include all HCV-positive randomized participants). We will examine potential rates of behavioral disinhibition as measured by changes in self-reported sexual risk (i.e., condom-less vaginal and/or anal sex), needle/works sharing, HCV infection/re-infection rates, and STI (including HIV) infection rates over the entire follow-up period. Additional analyses will examine the timing of initiation of both PrEP and HCV treatment, and whether non-engagement and discontinuation of PrEP are related to levels of (or changes in) risk.

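### A pooled HCV infection/re-infection outcome is compared between arms and read as behavioural disinhibition, although the cure co-primary itself changes who can be re-infected

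*Protocol article*

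**What the plan says.** Objectives (7) lists "HCV infection/reinfection" among the secondary outcomes on which the arms are to be compared, with behavioural disinhibition as a separate item.

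Table 4, under Outcomes (12), gives HCV incidence/re-infection one definition covering two at-risk groups: "HCV-Ab positive (never infected) or detectable HCV-RNA (previously infected and cured". In the same section, HCV cure (treatment started within 6 months and SVR by 12 months) is a co-primary outcome.

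Statistical methods (20a) describes how disinhibition will be examined. Beside self-reported sexual risk and needle or works sharing, it names "HCV infection/re-infection rates, and STI (including HIV) infection rates over the entire follow-up period". On the model it says "For all other secondary outcomes, similar approaches will be used", which refers back to Poisson regression for a binary outcome and its repeated-measures GEE version. The Discussion also presents HCV incidence as a good quantitative marker of injection risk.

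**The concern.** A participant with active HCV infection at entry cannot have a new infection under this definition until cured. Cure happens after randomisation and is what on-site care is meant to increase. Part of the risk set for this outcome is therefore produced by the treatment effect on a co-primary outcome.

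First infection and re-infection after trial cure are then pooled, compared by arm and read as behaviour. If on-site care cures more people, some of the arm difference reflects how many people could be infected, not how they behaved. A successful integrated-care arm could look as though it had raised injection risk. A real reduction in risk could also be hidden.

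**Working it through.** **Inputs from the protocol article**
- Sample size (14): "Our sample will include 500 participants in the PrEP component and approximately 240 in the HCV component". Sequence generation (16a): "Participants are randomized to one of two treatment groups in a 1:1 ratio". This gives 120 per arm in the HCV component and (500 − 240)/2 = 130 others per arm.
- Sample size (14): "We will utilize an alpha of .025 to account for our two co-primary outcomes", and for HCV cure "there is 90% power to uncover an absolute difference of 21% (40% versus 63%, RR = 1.58".

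**Inputs assumed**
- Infection hazards are not given. I use 5 to 20 per 100 person-years, and up to 30 for re-infection alone, always equal between arms.
- The 130 others per arm are taken as uninfected and at risk for the full 1.5 years.
- Time at risk after cure is 0.5 to 1.0 year, with 0.75 as the central value. Twelve weeks of treatment plus 12 weeks to SVR is about 5.5 months. Starting at month 0 leaves 18 − 5.5 = 12.5 months, and starting at month 6 leaves 18 − 6 − 5.5 = 6.5 months.

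**1. The plan's own figure.** Power for 40% versus 63%, 120 per arm, two-sided alpha 0.025 (sidedness is not stated) is 0.913, in line with the stated 90%. The printed difference of 21% does not match, since 63 − 40 = 23 points. With 40% versus 61%, two-sided power is 0.850 and one-sided power 0.907. Only 63% fits the printed risk ratio (0.63/0.40 = 1.575), so I use it.

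**2. Size of the re-infection risk set.** Off-site: 120 × 0.40 = 48. On-site: 120 × 0.63 = 75.6.

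**3. Re-infection per randomised HCV-positive participant.** Expected events = cured × (1 − exp(−λT)). With the same λ and T in both arms, the ratio is 75.6/48 = 1.575 whatever the hazard. At T = 0.75:

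| λ per 100 PY | Off-site events | On-site events | Ratio |
|---|---|---|---|
| 10 | 3.5 | 5.5 | 1.575 |
| 20 | 6.7 | 10.5 | 1.575 |
| 30 | 9.7 | 15.2 | 1.575 |

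The approximate chance of a nominally significant on-site excess (two-sided 0.05) is 6% to 27% over hazards of 5 to 30 and T of 0.5 to 1.0 year. The event counts are small, so this is rough. In the other direction, the on-site hazard would have to be about 38% lower (hazard ratio about 0.62) for the two proportions to come out equal.

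**4. The pooled outcome, 250 per arm.** Events = 130 × (1 − exp(−1.5λ₀)) + cured × (1 − exp(−0.75λ₁)), where λ₀ applies to the never infected and λ₁ to the cured. Person-years in each group = events/λ.

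| λ₀, λ₁ per 100 PY | Events, off-site v on-site | Ratio per randomised | Ratio per person-year |
|---|---|---|---|
| 5, 20 | 16.1 v 19.9 | 1.24 | 1.14 |
| 10, 10 | 21.6 v 23.6 | 1.09 | 1.00 |
| 20, 5 | 35.5 v 36.5 | 1.03 | 0.94 |

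The first and last rows are the extremes over hazards of 5, 10 and 20 in each group. The approximate chance of a significant on-site excess per randomised participant is 3% to 10%.

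**5. Person-time among the cured only.** At equal hazards the ratio is 1.00. The cured are, however, selected after randomisation by an outcome that the intervention is meant to change, so the comparison is no longer protected by randomisation.

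**The case against.** The article does not fix a per-randomised denominator. It speaks of rates, Table 4 defines the event by at-risk status, and Assessment of outcomes limits testing for new infection to people who were uninfected at their previous visit. A Poisson model can carry a person-time offset. Denominators for secondary outcomes are ordinary content for the analysis plan, which is not shown. All of this stands, and the missing denominator is not the fault raised here. It does not settle the matter, because the pooled definition and its behavioural reading are already in the protocol. Pooled person-time still shifts with the mix of never-infected and cured people (step 4), and a cured-only comparison is not randomised (step 5).

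HCV rates are also only one of several indicators. Table 4 measures disinhibition by self-report, and Objectives (7) defines it as the proportion who increase risk behaviour. That limits the harm, since a conclusion would not rest on HCV alone.

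Re-infections per randomised participant are a legitimate measure of net burden and may be useful for the transmission model. The problem is reading them as behaviour, not estimating them.

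A reader might infer that success on cure must produce a false harm signal, or that 1.58 is the bias in the outcome as defined. The documents support neither. The 1.58 belongs to re-infection alone, counted per randomised HCV-positive participant. Nor would an arm difference show that PrEP raises risk, because PrEP is offered in both arms.

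**Conclusion.** The point holds as a flaw in how a secondary outcome is built and interpreted. The arm comparison of pooled HCV infection/re-infection is not a clean measure of behaviour, because the cure co-primary determines part of its risk set.

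On the outcome as defined the effect is modest: a ratio of about 1.03 to 1.24 per randomised participant, and 0.94 to 1.14 per person-year, with no behavioural difference at all. The larger 1.58 appears only if re-infection in the HCV component is counted per randomised participant. The pooled ranges rest on the design cure rates, hazards of 5 to 20 per 100 person-years that are equal between arms, and 0.75 year at risk after cure. The 1.58 needs only the cure rates, equal hazards and equal time at risk. If the on-site cure rate were 61%, it would be 0.61/0.40 = 1.525.

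The co-primary analyses are not affected.

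**What to change.** - For the between-arm comparison read as disinhibition, use new HCV infection among participants who were HCV RNA-negative at randomisation. This group is defined at baseline, is at risk from day 0 in both arms, and is already tested every 3 months by antibody or RNA. It includes people who had cleared an earlier infection before entry.
- Keep re-infection after trial cure as a separate outcome, reported per person-year from first confirmed cure. The planned sequencing against stored baseline serum separates it from treatment failure. State that an arm difference in it will not be taken as evidence of changed risk behaviour.
- Amend the Table 4 row and the disinhibition sentence in Statistical methods (20a) to match, and carry both into the analysis plan.

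No new data are needed. The cost is precision. At 10 per 100 person-years in both groups, the randomised comparison would have about 18.1 events per arm (36.2 in all), against 21.6 + 23.6 = 45.2 for the pooled outcome, or about 20% fewer.
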